### 2.2. Design

As previous results of population wide prevention have been difficult to establish and this project takes place in the community, we choose an iterative, practice-based design that allows us to make ongoing adjustments during the implementation process. A participatory action research design fits the need for both responsiveness and a contextual approach. We will use mixed methods of data collection to gather insights in implementing public prevention in our healthcare system together with community members and Buurtzorg DN. The aim is that these insights allow all Buurtzorg teams to organise prevention programmes in their localities. Therefore, we will study the motivations of DN to work on prevention and the required qualities and knowledge of DN to successfully establish a prevention programme. The participatory action research approach allows us to immediately respond to the insights we gather during the project, so we can continue to evaluate and adapt the process during the project. For immersive collaboration with DN, every participating Buurtzorg team will choose one team member to be the co-researcher in this project, who will be in regular contact with the action researcher RK. As participatory action research is about doing research *with* instead of *on* people, these co-researchers will have a broad role in the entire project. They will be involved in data collection, reflections on the process of the study and their own experiences, contributing to the projects of other teams by sharing the lessons they learn along the way and helping to interpret the analysed data.

The study will consist of three phases. First, DN of each team will create an overview of their neighbourhood based on their prior knowledge, publicly available data, observations about the physical and social environment, networking with stakeholders and qualitative data gathered through interviews with community members. This overview will provide direction for possible health-related risks or issues in the neighbourhood that might be addressed in a local collective prevention project. In the second phase is the DN will, together with community members, prioritize and decide which subject to focus on. The third phase consists of designing and organising a collective prevention project in the locality together. The collaboration with community members in these steps is key to ensure that the programme is relevant to and created with the community, which are important preconditions for community building.

The time investment for the project as a whole, as well as the possible difficulties or delays in any of the phases will differ between the teams. Therefore, we use a stepped wedge design in this project. We will follow the teams and their prevention projects for 4–5 years, at the end of which we will be able to understand how collective prevention projects can be developed in collaboration with DN and community members, what the effective elements and obstacles are, and how it affects public health. The multimethod design ensures a rich and diverse representation of the impact of the collective prevention projects on the target audience. The quantitative effect measures will provide an indication of the change over time and possibly between groups. The qualitative measures in this study will provide a more detailed and personal image of health, well-being, motivations and other experiences during the project, as well as insight into elements that matter in the process. This will help to determine which projects can be considered successful and how they might be implemented on a larger scale.

### 2.3. Procedure

In the learning process of participative action research, qualitative methods can provide context specific and detailed information from the different perspectives of participants. Therefore, we keep the number of questionnaires to a minimum. Furthermore, long questionnaires can discourage community members from participating in the study, due to the time investment and possibly a perceived breach of their privacy. The general attitude of DN towards questionnaires is not positive either. They indicated that they prefer personal and informal communication with community members to build and maintain a relation of trust. After discussion, we have selected three questionnaires amounting to 18 questions in total and a selection of 17 questions from an annual employee questionnaire from Buurtzorg. We will start with a baseline measurement at the start of the project and repeat the data collection annually for four years, resulting in a total of four measurement times during the project.

During these four years, the researcher will conduct a number of interviews and focus group discussions to evaluate the process and gain insights in the experiences the DN and the community members during the project. These meetings will be voice- and/or video-recorded after permission from the participants. Observations about the atmosphere, non-vocal communication and other contextual information will be noted. In addition to the standard evaluation and measurements for every prevention project, we may deploy other methods for project specific outcomes in collaboration with the co-researchers. This will ensure that the methods suit the specific projects and their envisioned targets and that co-researchers are satisfied with the way their projects are evaluated.

Throughout the whole project, Buurtzorg teams will receive support from one of the three Buurtzorg coaches who are part of the project team for the organisation of the Collective Prevention programme. Additionally, the researcher will have monthly contact with the co-researchers to gather experiences from the team and evaluate the process of developing a collective prevention project. Finally, (participatory) observations will be made throughout the duration of the study, for example during brainstorm sessions, meetings or activities of the prevention projects.

In the first phase, the DN will gather information about people’s social situation and common health issues in the neighbourhood where they work by conducting at least 30 interviews with community members and health professionals such as general practitioners, physiotherapists and dietitians. DN will receive instructions and training for conducting interviews during webinars and workshops. The goal of these interviews is to determine what community members of every participating neighbourhood consider important aspects of public health in their lives and environment that may be improved by a prevention project. During this phase, the Buurtzorg teams will also ask permission and gather contact information from community members (and other stakeholders) who are willing to participate in this study. The researcher or co-researcher will explain the purpose, procedure, potential benefits and risks of participating in this study orally and in writing. We will also gather statistics about health problems and other relevant factors in the neighbourhood via publicly available data (such as the National Institute for Public Health and the Environment (RIVM) or Statistics Netherlands (CBS)). Based on this analysis, Buurtzorg teams together with community members will identify the topic for their prevention programme and develop a plan of action by again conducting (group) interviews and using design methods that will be discussed during monthly webinars.

### 2.4. Impact Measurement

An overview of the study design and the different measures in the study protocol can be found in Figure 1.

#### 2.4.1. Community Members

##### Health and Well-Being

Health and well-being of the community members will be evaluated by measuring two variables—quality of life and experienced health—annually in each project. Quality of Life will be measured using the validated Dutch ICECAP-O, the ICEpop CAPability measure for Older people, that consists of 5 items on a 4-point scale [43,44]. We use this measure that is specifically developed for older adults, because we expect that the majority of our study population will be older adults. Moreover, we expect that a capability approach, mapping both the capabilities in the environment as well as the degree to which members can take up these capabilities fit with the environmental approach of collective prevention. Experienced Health will be measured with the 4-item index of Perceived Physical Health [45]. These items are scored on a 5-point scale. The questions of this measure were translated from English to Dutch for the current project. We will use the WHO methodology for translation and adaptation of instruments to translate this instrument. In this methodology, we will translate and backtranslate the instrument after which we will pilot test it before using it for data collection in the whole study [46].

In the last year of the study, we will interview community members who participate in the prevention projects to gather qualitative data about health and social effects, their experience with the prevention projects and how it may impact their daily life. We will pose questions such as “What does preventive care mean for you?”, “How has the prevention project impacted your physical functioning, condition or energy level?”, and “What changes have you experienced in your social life or network since participating in this project?” (see Supplementary Materials, Topic list S1). Additional data about community members’ experiences in this project may come from (participatory) observation sessions throughout the 4 years of this study.

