#### 2.6.2. Qualitative Analyses

The qualitative data about the impact of the prevention programmes on health and well-being of community members, gathered during the focus groups, interviews and observations, will be transcribed and analysed using the qualitative data software programme MAXQDA (https://www.maxqda.com/, accessed on 8 February 2023). In order to account for subjectivity and personal errors, two researchers will be coding and analysing the data. We will determine which aspects of community members’ health, well-being, social and daily life are linked to participation in the prevention project by conducting an initial explorative content analysis, determining themes, followed by a more in-depth thematic content analysis. Observations and memos made during interviews about any contextual information (e.g., atmosphere) will be discussed between the interviewers and coders.

The analyses for the process evaluation, with the aim of determining effective elements, will be focusing on the observational data and data from focus groups and interviews with DN and community members. This analysis, as well as the analyses of DN’s motivation for and perspective on preventive work will be performed in the same way as described above.

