### 3.1. Implications

This study will provide information about which aspects of health, well-being and social life are affected by different collective prevention projects. As community members will be working together to organise activities, we expect that the impact of the prevention projects for community members will initially be measurable with our social effect measures. Initial participation may be a difficult step for many people, but once people are part of a group, it will be easier to take the initiative of going to other activities or outings in their daily life. This is expected to prevent or decrease loneliness and increase social participation, which has been shown to increase health and well-being [5,48,49]. The relations between people should be carefully considered and monitored to avoid negative effects on well-being due to failure of support, neglect or misdirection, which could lead to outcomes such as increased distress or decreased self-worth and self-efficacy [50]. The goal is to form a local social network with people helping and motivating each other and contributing to collective health goals by making use of each other’s talents. Ultimately, this may also lead to a decreased need for long term care or certain home care tasks. A stronger social network will also mean that people likely have better access to and knowledge of the available support systems and services, which will eventually lead to decrease in the workload of DN. This may contribute to better health care for the entire ageing population, because more people are able to maintain good health for a longer time with no or minimum help from DN. Consequently, DN can help more people without increase in the work hours.

All the prevention projects will be focused on a health-related issue or concern that Buurtzorg teams have identified together with community members. Therefore, this project is expected to improve health in the community. After identifying successful elements in the programme and viable projects, it could be implemented in other locations. It is a particular ambition of the study to use the lessons learned to implement collective prevention in all Buurtzorg teams (N = 950) in the Netherlands. Finally, the project aims to provide evidence for effective and sustainable bottom-up health care for other home care organisations and contributing to future-proof health care systems that fit an ageing population.

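### Two of the three published example questions for the last-year resident interviews take an effect of the project for granted, and no earlier interview on residents' own health is described to compare with

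*Protocol article*

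**What the plan says.** In the protocol article, 2.4.1 (Health and Well-Being), the effect interviews with residents are set at one time point: "In the last year of the study, we will interview community members who participate in the prevention projects to gather qualitative data". The data are to cover health effects, social effects, experience with the project and its effect on daily life.

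Three example questions are given, introduced by "We will pose questions such as":

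- one on what preventive care means to the person;
- one on health: "How has the prevention project impacted your physical functioning, condition or energy level";
- one on social life: "What changes have you experienced in your social life or network since participating in this project".

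The full list is in Supplementary Topic list S1, which is not among the documents at hand. Further data on residents' experiences "may come from (participatory) observation sessions throughout the 4 years of this study".

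Section 2.6.2 states the use of the material. The analysis will determine which aspects of residents' health, well-being, social and daily life "are linked to participation in the prevention project by conducting an initial explorative content analysis", followed by a deeper thematic analysis.

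**The concern.** The effect of the programmes on participants' health and well-being is the first primary objective (section 3, Discussion). The study has no control group (3.2), so part of the case for attributing change to the projects will rest on what participants say. Older people's health and social life can shift over several years for reasons unrelated to a walking group or a workshop.

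A question that names the project as the cause before establishing whether anything changed makes two answers harder to give: that nothing changed, and that something changed for another reason. If those answers are under-reported, the thematic analysis will find more aspects linked to participation than it should. According to section 2.2, the qualitative results help to decide which projects count as successful and how they might be scaled up. Section 3.1 names all 950 Buurtzorg teams as the ambition.

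**Working it through.** No figure in the document enters this point and no arithmetic applies beyond a count of questions and time points. The check sets the relevant sections side by side.

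**1. What each example question assumes**

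| Topic of question | Assumes an effect or change? | Assumes a direction? | Names the project? |
|---|---|---|---|
| Meaning of preventive care | No | No | No |
| Physical functioning, condition, energy | Yes | No | Yes, as the cause |
| Social life or network | Yes | No | Yes, as the starting point |

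Two of three assume an effect or change; none assumes benefit. The tilt is against no change, and not against a bad outcome.

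**2. Time points and wording, residents against nurses**

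| | Residents (2.4.1) | District nurses (2.4.2) |
|---|---|---|
| Individual interviews | Last year | First and last year |
| Content | Perceived health and social effects | Views, motivation, experience of the project |
| Balance of the published wording | Two of three questions assume an effect | One question asks for both good and less good aspects |

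The two sets of interviews have different purposes, so the comparison is not exact. It does show that both a two-point scheme and balanced wording are already in use in this study.

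**3. Does other material supply an earlier qualitative account of residents' own health?**

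- *Phase 1 interviews (2.3).* The teams gather information by "conducting at least 30 interviews with community members and health professionals such as general practitioners, physiotherapists and dietitians". The stated goal is to learn what matters for public health in the neighbourhood. Some interviewees are professionals, and nothing ties the residents interviewed to those who later take part. This is not an individual baseline.
- *Interviews and focus groups over the four years (2.3).* These include residents, but their purpose is to evaluate the process and learn about experiences. Residents' own functioning before joining is not mentioned.
- *Observations (2.3, 2.4.1).* They may record experiences and atmosphere, and no health record of individuals is described.
- *Annual questionnaires (2.3, 2.4.1).* Quality of life (5 items), experienced health (4 items) and social participation (9 items) make 5 + 4 + 9 = 18 questions, with a baseline and annual repeats. This is a real baseline, but a quantitative one. It shows whether scores moved and does not say what the person believes caused it.

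So change in the three scored outcomes is measured prospectively. The qualitative account of change, and of its cause, rests on recall at the end.

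**4. How the answers are used**

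Section 2.6.2 draws links to participation from focus groups, interviews and observations, with two researchers coding. A second coder guards against subjective coding. It cannot recover a no-change answer that the question did not invite.

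**The case against.** The strongest reply is that the interview is being judged from examples. Topic list S1 is not shown and may already contain neutral openers, no-change probes and questions on bad experiences. A trained interviewer can also follow up freely. This stands as a limit on the point: it applies to the published questions, and to S1 only where S1 does not already do better. The article nevertheless says that questions of this kind will be asked.

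A second reply is that one late interview on perceived effects, beside repeated questionnaires, is a legitimate choice in action research, and that 3.2 already cautions that effects cannot be attributed to project content alone. That is fair. The timing alone is not an error. It matters because it is combined with wording that presumes an effect.

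Some stronger readings are tempting, and the document does not support them:

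- *That reports of harm are discouraged.* Both questions are open in direction, so a negative answer fits either.
- *That there is no baseline at all.* The questionnaires provide one for the three annual outcomes.
- *That harm will be found only when it is too late.* Section 3.1 says "The relations between people should be carefully considered and monitored to avoid negative effects on well-being", but nowhere is the last-year interview presented as the means. Monthly contact with co-researchers, coaching (2.3), regular meetings where issues are raised and visits to activities (2.5) all run during the study.
- *That the phase 1 interviews could serve as the baseline without new contacts.* For the reasons given in the check, nothing in the document shows that the same residents would be reached.
- *That recall spans a fixed number of years.* Projects start at different times (2.2) and the social question asks about change since joining, so the span varies from person to person.

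**Conclusion.** The point holds in a limited form. Residents' effect interviews take place once, in the last year, with no matching earlier interview described on their own health. Two of the three published example questions presuppose an impact or change. In a study without a control group, whose analysis uses the answers to decide what is linked to participation, this tilts the qualitative evidence towards attributed effects and away from no change.

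The size of the tilt cannot be estimated from the document. The conclusion rests on two assumptions: that the published examples are representative of how the questions will be asked, and that S1 does not already correct the order and balance. If S1 does correct them, only the reporting recommendation remains. The point concerns wording and interpretation; it does not undermine the questionnaire analysis.

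**What to change.** **Reorder and reword the effect questions** (and S1, where it does not already do this):

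1. Ask how physical functioning, energy and social life are at present, without mentioning the project.
2. For each, ask whether it is better, about the same or worse than before the person joined.
3. Only where a change is reported, ask what the person thinks brought it about, with the project as one possibility among others.
4. Say explicitly that no change is a useful answer, and ask about unpleasant or disappointing experiences. The nurse interviews in 2.4.2 already seek both sides in this way.

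**In the analysis (2.6.2)**, code no change, and change put down to another cause, as categories of their own.

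**In the report**, describe the results as retrospective perceived change, and read each account alongside that participant's baseline and annual questionnaire scores. The planned within-subject analysis already requires each person's questionnaires to be linked. Setting the interview beside them assumes that the same study code is used for both.

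**Cost:** slightly longer interviews and a revised topic list. No new contacts or questionnaires are needed, and the interviews fall in the last year. Section 2.2 allows adjustments during the study. An added first-year interview on the nurse model would close the baseline gap more fully, but it costs extra fieldwork and is not needed for the rewording to be worthwhile.

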##### Social Participation

To study the social effects of the prevention projects and because of the focus on community engagement and building a social network in this project, we measure social participation. We chose this over other measures of loneliness or social isolation, because it is a broader outcome variable of social connectedness that participants may be more willing to talk about. We will measure social participation with a questionnaire consisting of 9 items from the participation section of the Social Domain Index. This is a Dutch survey from The Netherlands Institute for Social Research (SCP) that is used to measure national trends [47]. It consists of questions about participation in any clubs or associations, sports, volunteer work, theatre and more (see Supplementary Materials, Questionnaire S1). Four of these items are scored on a 4-point scale, 3 items require a yes/no answer and 2 items an estimate of the hours spent on a certain activity.

